**Secondary Objectives:**

- To evaluate impact of the VCT findings on patient management.
- To evaluate the cost of VCT for determining the aetiology of acute chest pain when compared to the standard care.

**Number of Subjects Planned:** 150

**Inclusion Criteria:** Subjects may be included in the study if they meet all of the following criteria:

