**Study Design:**

This study is designed as a single-centre trial to determine diagnostic value of VCT for differentiating cardiac from non-cardiac causes of acute chest pain in ED. Approximately 150 patients will be enrolled over a period of approximately 15 months.

The patient enrolment and study procedures are illustrated in the study flow charter, Figure 1.

Figure 1: Study Flow charter

Patients with acute chest pain presenting in ED

Initial Management by ED staff

- Clinical history
- ECG
- Chest X-ray
- IV line establishment and routine blood draw
- Medical therapy initiated

No or patient refuse

Standard care

No patient F/U

Eligible for enrollment?

Yes and patient consent

- Detailed history by research staff
- Additional blood for testing
- CT data available for clinical use when it is clinically needed
- The axial images and reconstructed image sets will be sent to core-lab for blinded evaluation

VCT scan

Two consensus readers review all clinical information and make diagnosis

- Routine care by primary physicians
- Additional imaging or lab tests
- Collection of medication, discharge diagnoses and cost information

Patient follow-up

**Study Imaging Tests:** Chest CT and cardiac CTA.

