**Cost Analysis:**

After hospitalization, the total cost will be estimated by total charges as established through the hospital billing office and physicias billing office. These costs will be compiled and compared to the current charge for a thoracic CT scan. A fictive cost will then be determined base on diagnosis and treatment using the CT results and that will be compared to the actual cost incurred by the patient without the CT results . The risk/benefit ratio will be compiled using the risk of complications due to the CT scan (such as renal insufficiency) to the diagnostic benefits of the scan.

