**Secondary Efficacy Endpoint(s):**

- Accuracy of VCT findings for triage patients to 1) implement appropriate therapy, 2) discontinue unnecessary/potentially harmful treatments, 3) limit observation time and diagnostic testing in the ED setting for acute chest pain.
- Potential cost saving using VCT to determine the aetiology of acute chest pain when compared to the standard care by changing patient management strategy.

**Safety Variables:** The following safety data will be collected and evaluated through the CT procedure:

- Unexpected adverse events
- Serious adverse events

**Gold Standard/Standard of Truth/Truth Panel:** Routine clinical information, including but not limited to, medical history, laboratory tests, ECG tests, other image tests and non-cardiac CT findings. To arrive at an adjudicated diagnosis, two board certified cardiologists independently reviewed all available evidence including history and physical, chest radiograph, non-cardiac CT findings, ECG’s, stress tests, cardiac catheterization, clinical follow up, and pharmacologic trials. Patients were categorized as ACS in the adjudicated diagnosis if 1) plasma troponin I >0.4 mg/dL during the index hospitalization, 2) a nuclear stress test with a summed difference score > 3, 3) an echocardiographic stress test with new or worsening dyssynergy in at least 1 ventricular segment, or 4) coronary stenosis >70% on catheterization. Each reviewer generated a prioritized adjudicated diagnosis list for each patient after the 3 month follow up data were available. Discrepancies between the reviewer’s lists were resolved by consensus. The highest priority consensus diagnosis was considered the cause of the patient’s symptoms for data analysis.

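### The standard-care cost contains charges caused by the study CT, so the reported cost saving is too large by up to twice any billed complication charge

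*Protocol*

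**What the plan says.** The protocol's Cost Analysis section defines both sides of the comparison.

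- Actual side: "the total cost will be estimated by total charges as established through the hospital billing office" and the physicians' billing office. No charge is excluded.
- CT side: "A fictive cost will then be determined base on diagnosis and treatment using the CT results".
- The comparison: "that will be compared to the actual cost incurred by the patient without the CT results".
- Complications: "The risk/benefit ratio will be compiled using the risk of complications due to the CT scan (such as renal insufficiency", the bracket closing there, set against the scan's diagnostic benefit. This is the only place in the section where complications appear.
- The section also compares the compiled costs with the going charge for a thoracic CT. It does not say that this charge is added to the fictive cost.

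Under Study Design, "Approximately 150 patients will be enrolled over a period of approximately 15 months", and the flow chart sends every eligible, consenting patient to the VCT scan. Patients who are ineligible or refuse receive standard care and are not followed up.

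The result feeds a secondary efficacy endpoint: "Potential cost saving using VCT to determine the aetiology of acute chest pain when compared to the standard care".

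**The concern.** The actual cost is described as cost without the CT results. That is not the same as cost without the CT scan. The results are largely withheld from the treating team, but the contrast, the pre-medication and any harm from them are not withheld from the patient. If the scan leads to a longer stay, extra laboratory tests or treatment, and these are billed, they enter the column that represents standard care. The protocol observes no cost from patients without a CT, so the data offer no correction.

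The fictive cost is described by what would follow from the CT information. Complications are recognised in the same section but sent to a ratio that is separate from the cost comparison. Read literally, the plan debits harm done by CT to standard care and does not debit it to CT. Cost reduction is one of the three study hypotheses, a secondary objective and a secondary endpoint, so a comparison tilted toward CT weakens a conclusion that the trial intends to draw.

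**Working it through.** The protocol states no cost, charge or complication rate, so there is no figure to reproduce. The bias can still be derived in units of the complication charge.

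**Definitions, for one subject**
- S: charges under standard care without the study CT.
- F: cost of the CT-guided strategy, leaving out the scan-caused charge.
- C: the charge caused by the scan.
- a = 1 if C is in the actual bill, otherwise 0.
- f = 1 if C is in the fictive cost, otherwise 0.
- d = 1 if the treating physicians judged a CT clinically indicated, so that C belongs to standard care as well; otherwise 0.

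**Formulas**
- Target saving = (S + dC) − (F + C)
- Planned saving = (S + aC) − (F + fC)
- Overstatement = planned − target = (1 − d + a − f)C

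**Numerical check.** Assumed values, for illustration only: S = 10,000, F = 6,000, C = 2,000. The multiples of C do not depend on them.

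| CT clinically indicated (d) | C in actual (a) | C in fictive (f) | Planned saving | Target saving | Overstatement |
|---|---|---|---|---|---|
| 0 | 1 | 0 | 12,000 − 6,000 = 6,000 | 10,000 − 8,000 = 2,000 | 4,000 = 2C |
| 0 | 1 | 1 | 12,000 − 8,000 = 4,000 | 2,000 | 2,000 = 1C |
| 0 | 0 | 0 | 10,000 − 6,000 = 4,000 | 2,000 | 2,000 = 1C |
| 0 | 0 | 1 | 10,000 − 8,000 = 2,000 | 2,000 | 0 |
| 1 | 1 | 0 | 6,000 | 12,000 − 8,000 = 4,000 | 2,000 = 1C |
| 1 | 1 | 1 | 4,000 | 4,000 | 0 |
| 1 | 0 | 1 | 2,000 | 4,000 | −2,000 = −1C |

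The unrestricted definition of total charges gives a = 1 for anything billed within the compiled charges. Where no CT was clinically indicated, that leaves the first two rows: 2C or 1C. The only unbiased allocation for such a subject is a = 0, f = 1, which the plan does not specify. The last row shows that removing C from the actual cost of a subject who needed a CT anyway would over-correct, against CT.

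**Averaged over subjects.** With complication rate r, the mean overstatement is rC at 1C and 2rC at 2C. Both r and C are assumptions.
- r = 1% and C = 2,000: 0.01 × 2,000 = 20 at 1C, 40 at 2C.
- r = 10% and C = 10,000: 0.10 × 10,000 = 1,000 at 1C, 2,000 at 2C.
- As a share of the average episode charge, with C between 0.5 and 1 episode and r between 1% and 5%: 0.01 × 0.5 = 0.5% up to 0.05 × 1 = 5% at 1C, and 1% to 10% at 2C.

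With 150 subjects, r of 1% to 5% means about 1.5 to 7.5 affected subjects, so the realised figure would rest on a handful of bills.

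**The case against.** The strongest objection is that the protocol never says the fictive cost leaves complications out. Naming them in a risk/benefit ratio does not exclude them elsewhere, and line-item costing rules are often left to a later plan. This stands in part. A reader might infer that the overstatement is always exactly twice the complication charge, and that the more harm the scan does, the larger the saving becomes. The text does not support either as a fixed result. The planned saving moves with C at the rate (a − f), so it grows with harm only when the charge is in the actual bill and absent from the fictive cost. What survives is the actual side: total charges are stated without restriction and every subject is scanned. Even if the fictive cost carries C, the saving remains C too large for a subject with no clinical need for a CT. That is a stated rule that misleads, not a detail left open.

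Four further objections have some force.

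- **Late complications may fall outside the bill.** Charges are compiled after hospitalization, and the Rationale gives 6 to 24 hours as the usual observation time. Renal insufficiency found after discharge may not be captured. Then a = 0, and the overstatement is C or nothing.
- **Some subjects would have had a CT anyway.** The section on image sequestering releases the images when the treating physicians find a CT clinically indicated. For them the charge belongs to standard care too, and any fix must allow for this.
- **The scan price is not ignored.** The section already refers to the thoracic CT charge. Whether the study scan itself is billed to the patient's account is not stated.
- **The harm may be rare.** The exclusion criteria cover known contrast allergy, raised creatinine and instability, and the preparation steps have blood-pressure limits. This bears on the size of the bias, not its direction.

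**Conclusion.** The concern holds in a limited form. As written, the standard-care cost includes whatever billed care the study CT caused. For a complication charge C within the compiled bill, in a subject with no clinical indication for a CT, the saving is overstated by C if the fictive cost also includes C, and by 2C if it does not. Where a CT was clinically indicated, the excess is C or zero. In all these cases any bias favours CT.

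The amount in money cannot be computed from the protocol. The range of 0.5% to 10% of an average episode charge rests wholly on assumed rates and charges and should not be read as an estimate. The primary diagnostic endpoint is unaffected. The point matters for the secondary cost endpoint of a single-centre pilot and is worth correcting because the remedy is cheap.

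**What to change.** Amend the Cost Analysis section so that:

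1. charges attributable to the study CT, its pre-medication and its complications are removed from each subject's actual cost, except where the treating physicians judged a CT clinically indicated, in which case they stay;
2. the fictive CT cost includes, for every subject, the scan charge (the thoracic CT charge that the section already names) and the charges for complications of the scan;
3. the saving is reported with and without this adjustment.

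The change needs a few sentences and a flag on line items in billing data that are already being collected. The downsides are a slightly smaller reported saving and some judgement in deciding which charges the scan caused.

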**Primary Efficacy Endpoint(s):**

Predictive values of VCT findings on differentiating cardiac from non-cardiac causes of acute chest pain in ED for determining 1) significant blockages in the coronary arteries that supply the heart, 2) evidence of dissection of the aortic tissues, 3) obstructive blood clots in the pulmonary arteries when compared to standard care information, and 4) other non-cardiac causes of chest pain.

**Secondary Efficacy Endpoint(s):**

- Accuracy of VCT findings for triage patients to 1) implement appropriate therapy, 2) discontinue unnecessary/potentially harmful treatments, 3) limit observation time and diagnostic testing in the ED setting for acute chest pain.
- Potential cost saving using VCT to determine the aetiology of acute chest pain when compared to the standard care by changing patient management strategy.

**Safety Variables:** The following safety data will be collected and evaluated through the CT procedure:

- Unexpected adverse events
- Serious adverse events

**Gold Standard/Standard of Truth/Truth Panel:** Routine clinical information, including but not limited to, medical history, laboratory tests, ECG tests, other image tests and non-cardiac CT findings. To arrive at an adjudicated diagnosis, two board certified cardiologists independently reviewed all available evidence including history and physical, chest radiograph, non-cardiac CT findings, ECG’s, stress tests, cardiac catheterization, clinical follow up, and pharmacologic trials. Patients were categorized as ACS in the adjudicated diagnosis if 1) plasma troponin I >0.4 mg/dL during the index hospitalization, 2) a nuclear stress test with a summed difference score > 3, 3) an echocardiographic stress test with new or worsening dyssynergy in at least 1 ventricular segment, or 4) coronary stenosis >70% on catheterization. Each reviewer generated a prioritized adjudicated diagnosis list for each patient after the 3 month follow up data were available. Discrepancies between the reviewer’s lists were resolved by consensus. The highest priority consensus diagnosis was considered the cause of the patient’s symptoms for data analysis.

**Statistical Methods:** The primary outcome is the diagnostic performance of CT compared to the standard of care to diagnose acute coronary syndrome (ACS). The classification accuracy of coronary CT to an adjudicated diagnosis for ACS. The diagnostic measures (e.g., sensitivity, specificity) for the CT diagnostic test for “significant CAD” (>50% stenosis) will be determined using the adjudicated diagnosis for ACS as the correct diagnosis. A >70% CTA stenosis will also be tested as a binary variable. Empiric confidence intervals will be calculated for each point estimate. Receiver operator classification (ROC) curves and area under the curve (AUC), both binary and empiric, will also be calculated. Classification accuracy between ECG-gating techniques (i.e., P-CT and R-CT) will be compared by relative probability estimates.

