**Primary Objective:** To evaluate the diagnostic performance of VCT for differentiation of cardiac from non-cardiac causes of acute chest pain in ED to determine presence or absence of 1) significant blockages in the coronary arteries that supply the heart, 2) evidence of dissection of the aortic tissues, and 3) obstructive blood clots in the pulmonary arteries when compared to standard care information.

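### The truth panel keeps one diagnosis per patient, but the primary objective and endpoint need each coexisting condition scored separately; the ACS label is also unsettled when another diagnosis ranks first

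*Protocol*

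**What the plan says.** The Primary Objective is framed condition by condition: CT is "to determine presence or absence of 1) significant blockages in the coronary arteries that supply the heart, 2) evidence of dissection of the aortic tissues". Obstructive pulmonary clot is the third item. The Primary Efficacy Endpoint follows it: "Predictive values of VCT findings on differentiating cardiac from non-cardiac causes of acute chest pain in ED for determining 1) significant blockages", then dissection, pulmonary clot and other non-cardiac causes. Under CT Image Evaluation/Procedures, the readers record coronary stenosis and the non-cardiac findings as separate items.

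The reference standard is in the paragraph headed Gold Standard/Standard of Truth/Truth Panel. It makes four statements that matter here:

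- The two cardiologists "independently reviewed all available evidence including history and physical, chest radiograph, non-cardiac CT findings", along with the other clinical evidence.
- ACS is defined by criteria: "Patients were categorized as ACS in the adjudicated diagnosis if 1) plasma troponin I >0.4 mg/dL during the index hospitalization", or if any one of three further criteria is met (nuclear stress test, stress echocardiography, catheterization). Rank is not mentioned.
- "Each reviewer generated a prioritized adjudicated diagnosis list for each patient after the 3 month follow up data were available". Differences are settled by consensus.
- "The highest priority consensus diagnosis was considered the cause of the patient", and the sentence goes on to say that this holds for data analysis.

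Statistical Methods details one accuracy analysis, CT stenosis against ACS. Its measures "will be determined using the adjudicated diagnosis for ACS as the correct diagnosis".

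**The concern.** CT can report several conditions in one patient, and the objective asks about each of them. The reference, as written for analysis, carries one label per patient. Nothing in the Protocol makes the conditions mutually exclusive, and asking for a ranked list accepts that a patient may have more than one. The Protocol does not say what sets the priority or how a lower-ranked diagnosis is scored.

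If the top diagnosis is the truth label, a patient listed as ACS first and embolism second is reference-negative for embolism. A CT that shows the clot is then charged with a false positive, although the panel itself accepted the embolism. Predictive values are the stated primary endpoint, and PPV for a rare condition rests on very few patients.

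For ACS the difficulty is of another kind. A patient who meets one of the four criteria but has another diagnosis ranked first is ACS under one sentence and not ACS under another. This label is the reference for the only accuracy analysis that Statistical Methods describes.

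**Working it through.** The Protocol gives no figure to reproduce on this point. It plans 150 patients and states no prevalence, coexistence rate, sensitivity or specificity. The rates below are assumptions, used to show direction and order of size.

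**Method.** Let N = 150, D = patients who truly have the condition, and k = those among them in whom it is ranked second. Assume that CT sensitivity (Se) is the same whatever the rank.

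- Scored from the full list: TP = D·Se, FN = D·(1−Se), FP = (N−D)·(1−Sp), TN = (N−D)·Sp.
- Scored from the top diagnosis only: k·Se patients move from TP to FP, and k·(1−Se) move from FN to TN.
- The number of CT positives does not change, so PPV is multiplied by (D−k)/D.

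**Embolism or dissection, Se = 0.90, Sp = 0.98 (expected counts).** Take D = 3, k = 1.

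- Full list: TP = 2.7, FP = 147 × 0.02 = 2.94, PPV = 2.7/5.64 = 0.48.
- Single label: TP = 1.8, FP = 2.94 + 0.9 = 3.84, PPV = 1.8/5.64 = 0.32.
- NPV: 144.06/144.36 = 0.998 becomes 144.16/144.36 = 0.999.

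| D | k | PPV, full list | PPV, single label |
|---|---|---|---|
| 2 | 1 | 0.38 | 0.19 |
| 3 | 1 | 0.48 | 0.32 |
| 3 | 2 | 0.48 | 0.16 |
| 5 | 1 | 0.61 | 0.49 |
| 5 | 2 | 0.61 | 0.36 |

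**A missed embolism.** Take 3 embolisms and no false positives; CT finds 2, and the missed one is ranked second. Sensitivity is reported as 2/2 instead of 2/3, and NPV as 148/148 instead of 147/148 (99.3%), a gain of 0.7 points. This can happen only if a source other than the study CT put the embolism on the list.

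**ACS, on the reading that rank decides.** Take 15 ACS patients, 3 of them ranked second, of whom CT finds 2 and misses 1, with 13 false positives among the other 135.

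| | Full list | Single label |
|---|---|---|
| Sensitivity | 13/15 = 0.87 | 11/12 = 0.92 |
| Specificity | 122/135 = 0.904 | 123/138 = 0.891 |
| PPV | 13/26 = 0.50 | 11/26 = 0.42 |
| NPV | 122/124 = 0.984 | 123/124 = 0.992 |

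On the reading that meeting a criterion is enough, a patient who meets one keeps the ACS label whatever the rank, and there is no shift. The text does not choose between the two readings. With k = 0 there is no shift for any condition.

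**The case against.** The best defence is that the single label answers a legitimate question. The endpoint speaks of telling cardiac from non-cardiac causes of pain, and one cause per patient is the natural reference for that. In addition, no sentence says outright that a second-ranked embolism is reference-negative, and the embolism and dissection tables may be set out in an SAP that is not at hand. This stands for the attribution part of the endpoint. It does not cover the presence-or-absence wording of the Primary Objective. Nor is the matter simply left open, because the Protocol itself fixes the top diagnosis as the one used for data analysis.

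A reader might infer more than the document supports:

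- *That coexisting ACS is certainly lost.* The four-criterion rule can be read as independent of rank, so this is one reading only. Separately, a CT stenosis without ACS is a false positive under Statistical Methods whatever the ranking rule.
- *That every missed embolism or dissection is hidden as a true negative.* The panel works partly from the non-cardiac CT findings, so a CT miss reaches the list only through other evidence.
- *That NPV is seriously inflated.* The change is under one point in every example worked here.
- *That all the rare-condition estimates suffer.* A demoted diagnosis affects only its own condition's table.

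A further caution concerns the remedy. Scoring ACS by criterion alone could label a patient ACS on troponin when the panel attributes the illness to embolism; a clear coronary CT would then count as a false negative. This is a reason to state the ACS rule explicitly, not to leave it in two versions.

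**Conclusion.** The point holds in a limited form. The Gold Standard paragraph applies a one-label reference to an objective and endpoint that are set condition by condition. For embolism and dissection, followed as written, a correct CT finding ranked second becomes a false positive. For ACS, the paragraph gives two incompatible answers for a patient who meets a criterion but has another diagnosis ranked first, so the reference for the Statistical Methods analysis is unsettled for such patients.

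The main effect is on PPV for rare conditions: 0.48 to 0.32 for one demoted case among 3 embolisms in 150, with sensitivity 0.90 and specificity 0.98. All of these inputs except the 150 are assumptions. The number of coexisting diagnoses cannot be derived from the Protocol and may be zero. The matter should be corrected because the primary endpoint depends on it and the correction is inexpensive; it does not invalidate the design.

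**What to change.** In the Gold Standard paragraph:

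1. Have the panel's consensus record ACS, aortic dissection, pulmonary embolism and other non-cardiac cause each explicitly as present or absent. Absence from a ranked list is not the same as an adjudicated absence, so the fields should be completed and not inferred.
2. Use each field as the reference for its own 2x2 table and its own predictive values.
3. State whether ACS counts when it is on the consensus list or when a criterion is met, in either case regardless of rank, and carry the same definition into Statistical Methods.
4. Keep the highest-priority diagnosis for a separate cause-of-symptoms analysis (cardiac versus non-cardiac), and state what sets the priority.

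The cost is a few sentences of wording and four fields for a panel that already reviews every patient's evidence. No further patient, test or reader is needed. The small drawback is that the condition tables no longer sum to one diagnosis per patient.

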**Rationale:**

Acute chest pain is a common and costly clinical condition accounting for over 5 million emergency department visits per year in the United States. In general, individuals presenting to the emergency department for chest pain require 6-24 hours of observation and multiple tests to differentiate pain from blocked heart arteries (i.e., acute or chronic coronary syndrome) from other non-cardiac sources.

Patient evaluation for cardiac causes typically includes sequential electrocardiograms and blood tests for heart enzymes to establish if a heart attack has occurred. Subsequently, cardiac stress testing or heart catheterization is required to firmly establish a diagnostic and treatment plan.

Non-cardiac but potentially life threatening illnesses can mimic cardiac symptoms and make an accurate diagnosis difficult, including a) blood clots in the lung vessels, or pulmonary embolism (PE), or b) a tearing of the vessel wall in the large artery supplying oxygenated blood to the body known as aortic dissection. These diagnoses are missed initially in the Emergency Room in up to 10% of patients presenting with acute chest pain. Failure to recognize these diseases often leads to delayed, unwarranted, or even detrimental medical treatments for these patients. Other non-cardiac causes of acute chest pain may include pneumonia, pleurisy, rib or other bone fracture, neuritis, or soft tissue injury.

Ideally, management of patients with acute chest pain would include a single test that is fast, easy to administer, widely and readily available at all times, and able to effectively differentiate many causes of acute chest pain. However, no single test currently exists.

CT is a widely available and standard imaging tool in Emergency Department (ED) that has been used for imaging applications throughout the body. CT angiography has been well studied and validated for identifying PE and aortic dissection when suspected, and is the preferred imaging modality for these diseases. Use of CT allows effective and timely evaluation for each of these potentially lethal diagnoses. CT can also effectively diagnose pneumonia, fracture, soft tissue injury, and may show signs suggesting pleurisy or neuritis. However, technical difficulties in imaging the moving heart and the size and motion of the small heart arteries (typically 4 to 1.5 mm and smaller) have been daunting for CT imaging.

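### Three of the four criteria for adjudicated ACS carry no acuity condition, so the primary ACS result can measure obstructive or ischaemic coronary disease, with PPV and specificity for ACS overstated

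*Protocol*

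**What the plan says.** Statistical Methods in the protocol names the target: "The primary outcome is the diagnostic performance of CT compared to the standard of care to diagnose acute coronary syndrome (ACS"). CT is positive for significant CAD at more than 50% stenosis, and its sensitivity, specificity and related measures "will be determined using the adjudicated diagnosis for ACS as the correct diagnosis". A stricter cut-off is added: "A >70% CTA stenosis will also be tested as a binary variable".

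The reference is defined under Gold Standard/Standard of Truth/Truth Panel. Four criteria are listed and joined by *or*:

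- The troponin criterion: "Patients were categorized as ACS in the adjudicated diagnosis if 1) plasma troponin I >0.4 mg/dL during the index hospitalization".
- The nuclear criterion: a summed difference score above 3 under stress.
- The stress-echo criterion: wall motion that becomes abnormal, or more abnormal, in one or more segments.
- The angiographic criterion: "or 4) coronary stenosis >70% on catheterization".

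The same paragraph then has each of two cardiologists rank the diagnoses once the 3-month follow-up is in. Differences are settled by consensus, and the top-ranked diagnosis is analysed as the cause of the symptoms.

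Elsewhere the coronary target is described differently. The Primary Objective and the Primary Efficacy Endpoint(s) speak of significant coronary blockages, and the endpoint is expressed as predictive values. The Rationale places "acute or chronic coronary syndrome" together on the coronary side, against non-cardiac causes.

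**The concern.** Only the first criterion, troponin during the index stay, marks an acute event. The other three show inducible ischaemia or a fixed narrowing. None requires that the finding be new, that the lesion be the culprit, or that it explain the index pain. A patient with long-standing stable disease can meet any of them.

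The entry criteria give this some weight. Patients with ST elevation, dynamic ST changes or troponin I above 2 mg/dl are excluded, which removes the clearest acute cases, while known CAD is not among the listed exclusions. The non-troponin criteria may therefore supply a material share of the ACS labels. The protocol gives no split.

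The fourth criterion also measures the same thing as the index test. For patients labelled ACS by catheterization alone, stenosis on CT is compared with stenosis on angiography, and agreement is counted as a correct diagnosis of ACS.

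At stake is what the trial can claim. A result reported as accuracy for ACS might really be accuracy for coronary disease in patients with chest pain. That is a legitimate target, and closer to the stated objective, but it is a different one.

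**Working it through.** The protocol gives no expected accuracy, ACS prevalence or derivation of the 150 patients, so there is no figure of its own to reproduce. The check compares two labels on the same expected data: the pooled label (any criterion met) and a symptom-attributed ACS label.

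**Notation.** a = patients with true ACS; c = patients with stable coronary disease only who meet one of criteria 2 to 4; n = all others. CT is positive in proportions Sa, Sc and f of these groups. P is the number of CT positives and M the number of CT negatives; both are the same under either label.

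**Pooled minus ACS label:**

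- PPV: (a·Sa + c·Sc)/P − a·Sa/P = c·Sc/P. Positive whenever any stable-disease patient is CT-positive.
- Specificity: c(Sc − f)/(n + c). Positive if Sc exceeds f.
- Sensitivity: c(Sc − Sa)/(a + c). Sign depends on whether Sc exceeds Sa.
- NPV: −c(1 − Sc)/M. Never positive.

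**Illustration.** N = 150 is the protocol's number. Everything else is assumed: 10% true ACS (a = 15), 5% stable disease only (c = 7.5), the rest n = 127.5; Sa = 95%, f = 10%, and Sc = 95% to begin with.

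- CT positives: 14.25 + 7.125 + 12.75 = 34.125. CT negatives: 0.75 + 0.375 + 114.75 = 115.875.
- PPV: pooled 21.375/34.125 = 62.6%; ACS 14.25/34.125 = 41.8%.
- Specificity: pooled 114.75/127.5 = 90.0%; ACS (114.75 + 0.375)/135 = 85.3%.
- Sensitivity: pooled 21.375/22.5 = 95.0%; ACS 14.25/15 = 95.0%.
- NPV: pooled 114.75/115.875 = 99.0%; ACS 115.125/115.875 = 99.4%.

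Varying only Sc (pooled vs ACS label, %):

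| Sc | PPV | Specificity | Sensitivity | NPV |
|---|---|---|---|---|
| 95 | 62.6 vs 41.8 | 90.0 vs 85.3 | 95.0 vs 95.0 | 99.0 vs 99.4 |
| 60 | 59.5 vs 45.2 | 90.0 vs 87.2 | 83.3 vs 95.0 | 96.8 vs 99.4 |
| 40 | 57.5 vs 47.5 | 90.0 vs 88.3 | 76.7 vs 95.0 | 95.6 vs 99.4 |

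**Wider grid, also assumed** (ACS 5–10%, stable only 3–10%, Sa 85–95%, Sc 40–95%, f 10%). Pooled minus ACS label, in percentage points: PPV about +6 to +43, specificity about +1 to +9, sensitivity about −37 to +7, NPV about −8 to 0.

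**The case against.** The strongest reply is that the truth-panel paragraph already contains a safeguard. Two cardiologists rank diagnoses with follow-up in hand, and the top one is taken as the cause. A patient with pneumonia and an old 75% stenosis could have pneumonia ranked first. A reader might infer from the four criteria that such a patient must be counted as ACS; the text does not go that far. What remains is that it also categorizes patients as ACS when a criterion is met, states no exception, and does not say which rule prevails.

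Second, the label is not simply incidental disease. Every patient has chest pain of recent onset, and criteria 2 to 4 are the only listed ones that can capture troponin-negative unstable angina. This stands, and it is why restricting ACS to the troponin criterion would be wrong.

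Third, one might infer that CT detects these cases almost by definition. That fits the catheterization criterion only. The nuclear and echocardiographic criteria are functional and can disagree with CT.

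Fourth, a reference that includes obstructive disease suits the objective and the Rationale, which groups acute and chronic syndromes. This also stands. It supports renaming the pooled reference, but not reporting it as ACS.

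Finally, tabulation by criterion can be left to a SAP. Which diagnosis counts as truth cannot, since the protocol itself fixes it. Withholding cardiac CT findings from the treating physicians limits bias in care but does not address acuity.

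**Conclusion.** The point holds in a limited form. Criteria 2 to 4 have no acuity or culprit condition, the protocol does not say whether they override the panel's ranking, and the resulting label is the reference for a primary outcome called ACS. As written, that outcome can measure detection of obstructive or ischaemic coronary disease.

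If stable-disease patients are labelled ACS, PPV for symptom-attributed ACS is overstated whenever any of them are CT-positive. Specificity is overstated if they are CT-positive more often than other non-ACS patients. In the illustration the gaps are about 21 and 5 percentage points. PPV matters most here because the primary endpoint is expressed as predictive values.

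A reader might go on to infer that CT accuracy for ACS is overstated in general, or that pooled sensitivity is inflated. The documents do not support that. Sensitivity rises only if CT is positive more often in stable than in acute cases, and it may fall; NPV, which bears on the rule-out hypothesis, cannot rise. The sizes rest on assumed prevalences and CT positivity rates; the directions follow from the algebra. If the panel's ranking does govern, the distortion largely disappears, but the protocol has to say so.

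**What to change.** In the truth-panel paragraph and Statistical Methods:

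1. Name the pooled reference *obstructive or ischaemic coronary disease or ACS*, in line with the Primary Objective and the Primary Efficacy Endpoint(s).
2. State that for the ACS analysis the panel's top-ranked diagnosis, an acute coronary cause of the index pain, governs over criteria 2 to 4 alone. Patients with troponin-negative unstable angina then stay in ACS by panel judgement.
3. Record for each patient which criterion or criteria were met.
4. Report the CT 2x2 table against both references, and base any claim about ACS on the second.

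This needs no new patients or tests: wording, one recorded item and one extra table. The price is precision. In the illustration the ACS table has 15 expected cases instead of 22.5, so at the same sensitivity its interval is wider by a factor of roughly √(22.5/15) = 1.22.
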